## Abstract

**Background:**

Surgical site infections (SSIs) are the second most common form of nosocomial infection. Colorectal resections have high rates of SSIs secondary to the inherently contaminated intraluminal environment. Negative pressure wound therapy dressings have been used on primarily closed incisions to reduce surgical site infections in other surgical disciplines. No randomized control trials exist to support the use of negative pressure wound therapy following elective open colorectal resection to reduce surgical site infection.

**Methods/Design:**

In this single-center, superiority designed prospective randomized open blinded endpoint controlled trial, patients scheduled for a colorectal resection via a laparotomy will be considered eligible. Patients undergoing laparoscopic resection will be enrolled but only randomized and included if the operation is converted to an open procedure. Exclusion criteria are patients receiving an abdominoperineal resection or a palliative procedure, as well as pregnant patients and those with an adhesive allergy. After informed consent, 300 patients will be randomized to the use of a standard adhesive gauze dressing or to a negative pressure wound device. Patients will be followed in hospital and reassessed on post-operative day 30. The primary outcome measure is SSI within the first 30 post-operative days. Secondary outcomes include the length of hospital stay, the number of return visits related to a potential or actual SSI, cost, and the need for homecare. The primary endpoint analysis follows the intention-to-treat principle.

**Discussion:**

NEPTUNE is the first randomized controlled trial to investigate the role of incisional negative pressure wound therapy in decreasing the rates of surgical site infections in the abdominal incisions of patients following an elective, open colorectal resection. This low-risk intervention may help decrease the morbidity and costs associated with the development of an SSI in our patients.

**Trial registration:**

NCT02007018 – clinicaltrials.gov; 5 December 2013

**Electronic supplementary material:**

The online version of this article (doi:10.1186/s13063-015-0817-8) contains supplementary material, which is available to authorized users.

## Background

Surgical site infections (SSIs) are the second most common type of nosocomial infection and represent a significant burden on the healthcare system [1, 2]. The morbidity, increased length of stay, delay in further treatment (adjuvant chemotherapy or radiation) as well as the significant psychological effects on patients has been well demonstrated in the literature [3, 4]. In 1998, the only cost-analysis related to SSI that was performed in a Canadian center was published. Here, Zoutman and colleagues demonstrated an average of US$4000 in additional costs per patient [5]. Resections of colonic and rectal segments have been associated with the highest rates of SSI amongst cases without perforation of gross intra-abdominal contamination, likely secondary to the inherently contaminated intra-luminal environment [6]. In such circumstances, despite best practice recommendations of pre-operative antibiotic use and aseptic operative technique [4], SSIs are reported at rates of 15 to 30 % [7, 8].

Few interventions beyond pre-operative antibiotic prophylaxis and aseptic technique have been shown to decrease rates of SSI. Negative pressure wound therapy (NPWT) is a relatively new treatment concept, initially reported on in 1997 by Morykwas et al. as a novel therapy for chronic wounds [9].

The first identifiable report in the literature on incisional NPWT (iNPWT) is a case-series from Gomoll et al. in the setting of orthopedic trauma. They demonstrated a decrease in serous exudative rates and good healing of incisions post-operatively [10]. Cardiac surgery patients are known to be susceptible to mediastinitis, associated with significant morbidity and mortality. A retrospective review of 57 such patients who received iNPWT was reported in 2009 whereby an absence of any sternal wound infections was demonstrated [11]. In 2011, Stannard randomized 263 blunt orthopedic trauma patients with high-risk tibial and calcaneal fractures requiring surgical stabilization to either usual care or iNPWT [12]. Here they demonstrated a relative risk of infection of 1.9 times higher in control patients with no significant difference in the injury severity scores of each group. In a recently published series, 27 patients, postabdominoperineal resection, with significant risk factors for wound infection had iNPWT applied to their perineal incisions until the fifth post-operative day [13]. When compared to a recent historical control group, a statistically lower rate of perineal SSI was detected in the intervention group. Furthermore, on multivariate analysis, when other risk factors were controlled for, the use of iNPWT was found to be protective against the outcome of perineal SSI. Finally, Matatov et al. performed a retrospective cohort study using the same NPWT dressing as the current proposal and found a significant difference (24 % versus 6 %) in SSI compared to standard dressing following 115 femoral cut-downs for vascular procedures [14].

Patients undergoing elective, open colorectal surgery are at a high risk of SSI. Given the significant patient morbidity associated with this complication, there is an identifiable need for an intervention to help decrease the rates of SSI in this patient population. Furthermore, there is a paucity of literature investigating the role of iNPWT in colorectal surgery. The objective of this study is to assess the role of iNPWT in patients undergoing an elective, open colorectal resection (CRR) on decreasing the rates of SSI as compared with a standard gauze adhesive dressing. We hypothesize that patients randomized to iNPWT will have a lower incidence of SSI within the first 30 days of surgery compared to patients randomized to the control group. The trial will be a prospective, randomized, superiority trial.

## Methods/Design

A prospective analysis of SSIs at our institution was done to prepare the calculation of power and sample size, and informed the trial protocol and manuscript creation. Our institutional ethics at the University of Western Ontario performed a Full-Board review and approved the trial (REB 104819). The trial is registered at Clinicaltrials.gov (NCT02007018). This protocol conforms to SPIRIT recommendations for the minimum set of scientific, ethical, and administrative elements that should be addressed in a clinical trial protocol (Additional file 1). Financing is granted through an industry grant with Kinetic Concepts Inc. (San Antonio, TX, USA). The study sponsor has no role in data collection, management, analysis, writing or influence on the decision to publish results.

### Study design

This is a single-institution, prospective, randomized, open label, blind endpoint trial design [15] with a superiority framework, in which eligible patients will be randomized to iNPWT or a standard gauze adhesive dressing using block randomization and stratification based on one of two hospital sites.

### Study setting

The study will take place at the two campuses of London Health Sciences Center (LHSC) in London, Ontario, Canada: University Hospital and Victoria Hospital. Both hospitals are academic teaching hospitals and are associated with the Schulich School of Medicine and Dentistry at Western University. Both sites use an enhanced recovery after surgery protocol following colorectal surgery to improve patient outcomes and reduce length of stay [16].

### Eligibility

Patients scheduled for any elective CRR requiring a midline laparotomy are potentially eligible for the study. Patients booked for a laparoscopic approach are eligible to be enrolled but will only be randomized and included if their surgical procedures are converted to open through a midline laparotomy. Eligible surgical procedures include segmental, sub-total or total colectomies as well as low and ultra-low anterior resections. Before enrollment informed consent will be obtained from each patient. Patients will be identified by study personnel and will be enrolled from the pre-operative clinic by a study nurse.

### Inclusion criteria

Patients must be 18 years or older and scheduled for an elective CRR and must undergo an open procedure or laparoscopic procedure converted to open operation. Informed consent must be obtained.

### Exclusion criteria

Patient who undergo abdominoperineal resections and pelvic exenterations, or have a bowel perforation at the time of operation will be excluded. Patients undergoing an operation for palliative purposes (life expectancy less than 3 months), who are pregnant, or who have a known sensitivity/allergy to adhesive material will also be excluded.

### Intervention and control

The intervention addresses the type of dressing applied following an elective, open, colorectal operation. The intervention is iNPWT in the form of the Prevena™ Incision Management System (PIMS) (Kinetic Concepts Inc. (KCI), San Antonio, TX, USA). This is a sponge dressing connected to a hand-held continuous vacuum in a single-use unit. The vacuum is set to 125 mm Hg. The device is applied under sterile conditions in the operating theater and remains on the patient until the earlier of post-operative day 5 or hospital discharge. Any concern about the wound or the device will require removal of the iNPWT earlier than planned, and will be recorded as a secondary endpoint of the trial.

The control dressing is a gauze adhesive dressing which covers the laparotomy incision. The post-operative management is typically removal on day 2 post-operatively with daily dressing changes thereafter. Apart from the dressing applied to the wound in the operating room, and the care of that dressing post-operatively, the patients pre- and post-operative care will be the same in both groups.

As per current best practice in SSI prevention, the following regimen will be applied to all trial patients, regardless of intervention arm. A standardized dose of pre-operative antibiotics (depending on allergy status) directed by the hospital’s local antibiogram will be administered to patients within 30 minutes prior to surgery, and will be re-dosed in procedures longer than 4 hours. Post-operative antibiotics will be allowed for a maximum of 24 hours. Hair will be removed with electric clippers. Skin preparation will be performed with 2 % chlorhexidine unless the patient has an allergy to this preparation.

### Randomization, allocation concealment and blinding

Randomization will take place centrally using random permutated blocks of 4, 6 or 8 and will be stratified based on site (University Hospital or Victoria Hospital) of the operation. After the fascia is closed a member of the surgical team will use a centralized web-server to randomize the patient. The surgical team, clinical staff, and patient will not be blinded to the intervention status. The primary outcome of SSI will, however, be blinded to the outcome assessors, as the dressing (iNPWT or adhesive gauze) will be removed by the clinical team prior to the first visit from the outcome assessors on post-operative day 5 or the day of hospital discharge. The outcome assessors are blinded and will assess the wound daily after the dressing is removed until hospital discharge. A minority of wounds are expected to be seen by the on-call team and it is unlikely the resident or physician involved will know the patient’s treatment allocation.

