### Definition of endpoints and outcome measures

The primary endpoint is the incidence of SSI within 30 days of surgery. SSI is defined by the Center for Disease Control and Prevention (CDC) criteria [1] as: infection occurring within the first 30 post-operative days with at least one of the following:Purulent drainage from the incisionOrganisms isolated from an aseptically obtained culture of fluid or tissue from the incisionAt least one of the following signs/symptoms of infection:Pain or tendernessLocalized swellingRednessHeat

In these instances, the incision is deliberately opened by a surgeon (unless the incision is culture negative)4.Diagnosis of SSI by the surgeon or attending physician.

SSI will be assessed every day following dressing removal, at discharge, 30 days following the operation or at any time during the study period if the patient or surgical team has concerns about the development of an SSI in the laparotomy incision.

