### Sample size

Our pilot study revealed an SSI rate of 35 % in patients undergoing colorectal surgery at our institution. Based on previous studies and the clinical experience of the study’s senior investigators, a reduction in the rate of SSI to 20 % (absolute risk reduction 15 %; relative risk reduction 43 %) may be expected. This is the minimum clinically relevant reduction both from a patient outcome perspective and a cost reduction standpoint. Given an alpha of 0.05, for 80 % power, this yields a required sample size of 138 patients per group. The planned sample size will be inflated for potential loss of follow-up, and will be rounded for a final sample size of 150 patients per group and a total study sample of 300 patients. Loss to follow-up is felt to be a minimal concern as patients are required to attend their 30-day post-operative visit to maintain the therapeutic relationship with the surgeon for oncological and disease management.

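### Triggering randomization at fascial closure permits the unblinded surgical team to know the arm before the subcutis and skin are closed

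*Protocol article*

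**What the plan says.** Under *Randomization, allocation concealment and blinding* the protocol article sets the moment of allocation: "After the fascia is closed a member of the surgical team will use a centralized web-server to randomize the patient". It then adds: "The surgical team, clinical staff, and patient will not be blinded to the intervention status".

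*Intervention and control* defines the intervention as the type of dressing. On the negative pressure device it says: "The device is applied under sterile conditions in the operating theater". Its equal-care sentence opens "Apart from the dressing applied to the wound in the operating room, and the care of that dressing post-operatively" and concludes that "the patients pre- and post-operative care will be the same in both groups". A further statement, "the following regimen will be applied to all trial patients, regardless of intervention arm", introduces a list of prophylactic antibiotics, their re-dosing and post-operative limit, hair clipping and skin preparation. Closure of the subcutis and skin is in neither the equal-care sentence nor the list.

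The outcome is set under *Definition of endpoints and outcome measures*: "The primary endpoint is the incidence of SSI within 30 days of surgery". The criteria concern the incision, and the same section speaks of infection in the laparotomy incision.

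**The concern.** The randomized comparison is meant to isolate the dressing. In a midline laparotomy the subcutis and skin are ordinarily closed after the fascia and before any dressing goes on. If the arm is known by then, the people closing the wound can, without intending to, handle those layers differently in the two groups. Those layers form the incision in which infection is later judged.

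Such a difference would be performance (co-intervention) bias: it would arise after allocation and because of it. Blinded assessors protect the detection of infection, not the way the wound was closed. Intention-to-treat analysis keeps patients in their randomized groups, but it cannot separate a closure effect from a dressing effect.

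Once the dressing is in place, the team's knowledge of the arm is unavoidable, and the *Discussion* calls incomplete blinding the major limitation. Between fascia and skin that knowledge can be avoided.

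**Working it through.** **1. The plan's own figure.** *Sample size* takes 35% against 20%, alpha 0.05 and 80% power, and states 138 per group. Sidedness is not given; a two-sided test reproduces the figure. With pooled variance under the null and mean rate 0.275:

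n = [1.960 × √(2 × 0.275 × 0.725) + 0.842 × √(0.35 × 0.65 + 0.20 × 0.80)]² / 0.15²

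= [1.960 × 0.6315 + 0.842 × 0.6225]² / 0.0225 = 137.9, rounded up to 138.

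Power is 80.0% at 138 per group and 83.2% at the planned 150. The figure is sound and does not depend on when the arm is released.

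**2. The sections side by side.**

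| Question | What the article states |
|---|---|
| Earliest moment of allocation | After fascial closure |
| Latest moment | Not stated |
| Who randomizes | A member of the surgical team, which is unblinded |
| Care declared equal | Before and after the operation |
| Measures fixed for both arms | Antibiotics, clipping, skin preparation |
| Superficial closure | Not mentioned |
| Where infection is judged | The incision |

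Allocation before skin closure complies with these rules, and so does allocation after it. The rule permits early knowledge of the arm but does not require it.

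**3. Would later release lose anything?** *Eligibility* and *Exclusion criteria* turn on conversion to open surgery, type of procedure and perforation. All are known by fascial closure and are still known at skin closure. The document gives no reason for releasing the arm at the earlier moment.

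**4. Scale, by assumption only.** The document gives no closure effect. The shift between arms is the share of one arm whose closure changes, multiplied by the change in infection risk in those patients. If both lie between 0.10 and 0.20, the shift is 0.10 × 0.10 = 1 point to 0.20 × 0.20 = 4 points. Neither range comes from the document.

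For a shift b at 150 per group there are two cases:

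- *No dressing effect:* rates of 0.35 and 0.35 − b. The rejection probability is Φ[(b − 1.960 × se₀)/se₁] + Φ[(−b − 1.960 × se₀)/se₁], with se₀ the pooled and se₁ the unpooled standard error.
- *True 15-point effect, shift opposed to it:* power at 0.35 against 0.20 + b.

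For b = 0.03 with no dressing effect, se₀ = √(2 × 0.335 × 0.665/150) = 0.0545 and se₁ = √((0.35 × 0.65 + 0.32 × 0.68)/150) = 0.0545. The two terms are 0.079 and 0.006, total 0.085.

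| Assumed shift | Rejection rate, no dressing effect (nominal 5%) | Power, shift opposing a true 15-point effect (83% without shift) |
|---|---|---|
| 2 points | 6.5% | 71% |
| 3 points | 8.5% | 63% |
| 5 points | 15% | 47% |
| 8 points | 32% | 26% |

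The 5- and 8-point rows lie beyond the 1 to 4 point range and show only how the effect grows.

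**The case against.** There is a good case for the existing rule. Randomizing after fascial closure is already late: conversion, procedure and perforation are settled, exclusions after randomization are limited, and the arm is unknown throughout the resection. The equal-care sentence makes the dressing its only exception in the operating room, which shows an intent that nothing else should differ. A closure technique is also a detail that a journal article may leave to the full protocol. All of this stands, and it keeps the point small. It does not change the trigger, which the article does state.

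A reader might go further in four ways that the document does not support:

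- *That the arm is revealed before the skin is closed.* The text sets only an earliest time. Early release is the natural surgical reading, but it is an inference.
- *That closure will differ by arm.* Nothing shows this. The *Abstract* describes these devices as used on primarily closed incisions, which makes some influence on closure conceivable but is not evidence of it.
- *That the assessors could not see a difference.* They inspect the wound after the dressing is removed, so a different skin closure would often be visible. Irrigation and subcutaneous steps would not. Seeing a difference would not correct for it.
- *That the bias favors the device.* Extra care in the control arm would pull the result toward no difference; extra care in the device arm would exaggerate the benefit.

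**Conclusion.** The point holds as a minor one. The stated trigger, together with an unblinded team, permits the arm to be known while the incision may still be open, and no safeguard in the article covers that interval. The result is an avoidable route to performance bias on an incisional endpoint.

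Its size and direction are unknown. Under the assumed 1 to 4 points, the upper end would be 4/15, about 27% of the 15-point target, but that multiplies two upper guesses. The conclusion rests on the usual order of closing a laparotomy and on the article alone; a closure standard in the full protocol would reduce the concern further. The sample size is unaffected.

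**What to change.** Change one sentence and one step in the web procedure: the server releases the arm only after the team confirms that skin closure is complete, immediately before the dressing is applied. Eligibility is still settled before allocation, and neither the number of patients nor clinical care changes. The cost is a short wait before the dressing is opened.

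Entering the planned closure in the web form before release is a weaker alternative: it would let a departure be detected but would not prevent it.

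*Trial status* says that enrollment began on 5 January 2015, so an amendment would protect only patients randomized after it.

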### Definition of endpoints and outcome measures

The primary endpoint is the incidence of SSI within 30 days of surgery. SSI is defined by the Center for Disease Control and Prevention (CDC) criteria [1] as: infection occurring within the first 30 post-operative days with at least one of the following:Purulent drainage from the incisionOrganisms isolated from an aseptically obtained culture of fluid or tissue from the incisionAt least one of the following signs/symptoms of infection:Pain or tendernessLocalized swellingRednessHeat

In these instances, the incision is deliberately opened by a surgeon (unless the incision is culture negative)4.Diagnosis of SSI by the surgeon or attending physician.

SSI will be assessed every day following dressing removal, at discharge, 30 days following the operation or at any time during the study period if the patient or surgical team has concerns about the development of an SSI in the laparotomy incision.

### Secondary endpoints

Secondary outcomes assessed will include the need for, and duration of at-home nursing care (home care) related to SSI. The need for home care will be determined by the surgical team after the identification of an SSI. The duration of home care requirements will be determined at the time of post-operative clinic visits, and by contact with the home care provider. Additional secondary outcomes assessed will include the length of hospital stay, the number of return visits related to a potential or actual SSI, and cost. The cost will be determined based on the average cost provided by LHSC for inpatient, emergency department (ED) or clinic care, and billing fees for both the surgeon and anesthetist for any return trip to the operating room. Standardized time and materials costs will be obtained using available data from the Community Care Access Center for home care. A return visit related to an SSI will include any visit to the ED, outpatient surgical clinic, or requirement for admission to hospital that is deemed by the primary surgeon or study team to be due to a) signs or symptoms of SSI requiring assessment; b) development of an SSI requiring management; or c) ongoing care of a known SSI. The management cost of an SSI will be calculated for each instance. Outcomes related to potential harm will also be identified including local reaction to the iNPWT device, and the need for early removal of the dressing.

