### Data collection and management

All data collected (baseline characteristics, primary and secondary outcomes) will be recorded through an online data collection portal and be maintained behind a secure server and firewall. Data will be collected by the study nurse, trial personnel and surgical teams. A Data Safety and Monitoring Board (DSMB) will be assembled consisting of three surgeons not involved in patient accrual or in study administration. Given previous demonstration of the safety of iNPWT, we expect minimal to no harm. Accuracy of data collection through the online secure data collection forms will be ensured by the DSMB by performing sample assessments at regular intervals. The severity of adverse events will be evaluated using the Common Terminology Criteria for Adverse Events (CTCAE) v4.0 grading scale (see http://ctep.cancer.gov). Any grade 4 or grade 5 events will be reported to the primary investigator, the DSMB, and the institutional research ethics board as well as the device company headquarters through established reporting systems.

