Secondary outcomes will be compared between groups using a chi-square for categorical variables (i.e., need for home care, proportion receiving antibiotics). Non-normally distributed continuous variables (length of hospital stay, duration of home care treatment, number of return visits) will be compared using the Mann-Whitney *U*-test. As potential harm is expected to be minimal, incidence of allergy/sensitivity to iNPWT will be reported, but no formal statistical analyses are planned. A *p*value of less than 0.05 will be considered significant. The trial will undergo only one set of analyses at trial completion. No interim monitoring is planned as, given the small sample size, any interim analysis would have too few events to be interpreted. Recruitment will be completed over 12–16 months, and given that the primary outcome has occurred by 30 days after the last patient is randomized, primary outcome assessment will have occurred by 18 months. Allowing for prolonged data collection for up to 3 months for secondary outcomes, the trial analyses will be completed less than 21 months after the trial commences.

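### Local reaction and allergy/sensitivity are defined and reported for the iNPWT arm only, so their excess over the adhesive gauze dressing cannot be estimated from the stated analysis

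*Protocol article*

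**What the plan says.** All references are to the protocol article.

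- **Secondary endpoints** names the potential harms as "local reaction to the iNPWT device, and the need for early removal of the dressing". The first item is tied to the device. The second does not say which arm's dressing is meant.
- **Intervention and control** ties early removal to one arm: "Any concern about the wound or the device will require removal of the iNPWT earlier than planned, and will be recorded as a secondary endpoint". For gauze it says only: "The post-operative management is typically removal on day 2 post-operatively with daily dressing changes thereafter". No early-removal outcome is attached to it.
- **Statistical analysis** fixes the reporting: "incidence of allergy/sensitivity to iNPWT will be reported, but no formal statistical analyses are planned".
- The comparator is itself adhesive: "The control dressing is a gauze adhesive dressing which covers the laparotomy incision". Known adhesive allergy excludes a patient from the whole trial (**Exclusion criteria**).
- **Data collection and management** adds a general provision not limited to one arm: "The severity of adverse events will be evaluated using the Common Terminology Criteria for Adverse Events (CTCAE) v4.0 grading scale". The stated reporting route starts at the top grades: "Any grade 4 or grade 5 events will be reported to the primary investigator, the DSMB", and on to the ethics board and the device company.

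**The concern.** A gauze patient who reacts to the adhesive cannot, by definition, have a local reaction to the iNPWT device or an allergy to iNPWT. Yet both arms carry an adhesive dressing on the same incision, so some reactions seen under iNPWT would have occurred under gauze as well. A percentage from the device arm mixes that background with whatever the device adds.

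The error can run either way: ordinary adhesive reactions may be charged to the device, or a real excess may go unmeasured. Meanwhile the benefit is to be reported as an absolute risk difference with a number needed to treat. A reader weighing a preventive dressing would have a randomized estimate for infection and an uncontrolled one for local reaction. The Discussion expects the trial to inform consensus recommendations, so the contrast would be useful, and the randomization already makes it available.

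**Working it through.** **The group size used below.** The plan's 138 per group reproduces. With 35% vs 20% (mean 0.275), two-sided alpha 0.05 and 80% power:

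n = [1.96·√(2·0.275·0.725) + 0.8416·√(0.35·0.65 + 0.20·0.80)]² / 0.15² = (1.2377 + 0.5239)² / 0.0225 = 137.9, so 138.

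This is raised to 150 per group. The figure is not in dispute; it only supplies the denominator.

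**Which arm each harm item covers**

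| Item | iNPWT | Gauze |
|---|---|---|
| Local reaction (Secondary endpoints) | defined | not defined |
| Allergy/sensitivity (Statistical analysis) | to be reported | not mentioned |
| Early removal (Intervention and control) | endpoint | no counterpart |
| Early removal (Secondary endpoints) | arm not stated | arm not stated |
| CTCAE grading (Data collection and management) | not limited by arm | not limited by arm |
| Comparison of adverse events by arm | not stated | not stated |

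**What a one-arm count can and cannot say.** The documents give no local-reaction rate, so all counts here are assumptions. With 15/150 on iNPWT, the device arm alone gives 10.0% (exact 95% CI 5.7% to 16.0%). Counting the same event on gauze would give these differences (Newcombe 95% CI):

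| Gauze count | Excess, points | 95% CI |
|---|---|---|
| 0/150 | +10.0 | 5.4 to 15.8 |
| 3/150 | +8.0 | 2.7 to 14.0 |
| 8/150 | +4.7 | -1.5 to 11.1 |
| 15/150 | 0.0 | -7.0 to 7.0 |

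Worked for the first row: the Wilson limits are 0.0615 to 0.1584 for 15/150 and 0 to 0.0250 for 0/150. Lower limit: 0.10 - √[(0.10 - 0.0615)² + 0.0250²] = 0.054. Upper limit: 0.10 + (0.1584 - 0.10) = 0.158.

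The same device-arm result therefore fits an excess from 0 to 10 points, depending on a count that the stated analysis does not include.

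**Rarer events.** With 6/150 (4%) on iNPWT and 3/150 (2%) on gauze, the difference is 0.02 and SE = √(0.04·0.96/150 + 0.02·0.98/150) = 0.0197. The 95% CI is 0.02 ± 1.96·0.0197, about -2 to +6 points. With 0/150 on gauze the difference is 4 points. With no reactions among 150 iNPWT patients, the exact two-sided upper limit is 1 - 0.025^(1/150) = 2.4%.

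**Would a test help?** Power at 150 per arm, for assumed reaction rates: 10% vs 2%, 83%; 10% vs 3%, 69%; 10% vs 5%, 38%; 5% vs 1%, 53%. An estimate with an interval is the more useful summary, so the decision not to test is defensible.

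**The case against.** Most of the case on the other side stands, and it limits the point.

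- **A reader might infer that harms are recorded only in the iNPWT arm.** The text does not go that far. The harm list in Secondary endpoints is open-ended, its second item is not tied to an arm, and the section on randomization and blinding uses the same noun for both dressings. CTCAE grading is arm-neutral, so a gauze reaction could be captured there. The case report form is not shown. What remains is that only grades 4 and 5 have a stated reporting route, which a local skin reaction would seldom reach, and that no tabulation by arm is stated.
- **A reader might infer that the trial cannot show whether the device adds harm, or that its benefit-harm balance is unreadable.** That is too broad. SSI is reported as an absolute increase or reduction, and return visits, home care and length of stay are compared between arms. Harm through worse wound outcome is therefore estimated. Only the named local harms lack a contrast.
- **Early removal has no clean control equivalent.** Gauze typically comes off on day 2 and is then changed daily, whereas the device stays until day 5 or discharge. Comparing removals would compare unlike things.
- **An article condenses a fuller protocol.** True, and silence alone would be no finding. Here, however, the harm definition and the planned report are both affirmatively worded for one arm.
- **A two-arm count has limits.** Adhesive allergy is an exclusion, so rates may be low. Reactions during wear would be noted by unblinded staff, because the blinded assessors first see the wound after dressing removal. The interval may be inconclusive.

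**Conclusion.** The point holds in a limited form. Local reaction and allergy/sensitivity are defined and planned for reporting for iNPWT only, although the comparator is also adhesive, so their excess over gauze cannot be estimated from the analysis as stated. CTCAE grading softens this but does not cure it.

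The size is unknown because no reaction rate is given. Under the assumed counts, one device-arm figure of 10% is compatible with an excess of anywhere from 0 to 10 points. This rests on reading the harm definition and the reporting sentence as they stand; a by-arm table in the full protocol or analysis plan would settle it.

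This is a worthwhile improvement of minor severity. The primary analysis and the sample size are unaffected. Omitting a significance test for harm is not a fault. The documents do not support a claim that harm in general goes uncompared or that gauze reactions will certainly go unrecorded.

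**What to change.** 1. Replace the device-specific wording with one definition of local skin or adhesive reaction, applied identically in both arms over the same post-operative days.
2. Report the counts by arm with a risk difference and 95% CI, without a significance test. State that reactions during wear are recorded by unblinded staff.
3. Keep early removal as a descriptive outcome for the device only, and label it so. Reconcile Secondary endpoints, which does not say which dressing is meant, with Intervention and control, which names the iNPWT.

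The cost is one or two case report form items completed for control patients too. Sample size and primary analysis do not change. The price in inference is an imprecise interval at 150 per arm and some risk of ascertainment bias from unblinded recording; both should be stated with the result.
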